# Statement of Purpose and Background

| Discuss relevant background information and literature reviewed to provide the rationale for the proposed research. State the relevance of this research to and potential for contribution to the field of study. Provide justification for involving humans in the research. If relevant, include a summary of pre-clinical/animal data that have been obtained through other research. Please refer to section 4.4 of the IRB Guidebook for guidance on the information to include in this section.  The 1996 Surgeon General’s report on Physical Activity and Health summarized the effect of physical activity (PA) on prevention of morbidity and mortality.1 Physical inactivity is associated with an increased risk of cardiovascular mortality, a substantially higher risk of stroke and coronary heart events, and an increase of both systolic and diastolic blood pressures. 2, 3 Regular physical activity is protective of some cancers, specifically colon and breast cancers.4 The greatest gain in the prevention of all cause mortality appears to occur between inactivity and initiation of moderate intensity physical activity.5  Type 2 diabetes is a risk factor for heart disease and stroke and contributes to over 220,000 deaths a year and $132 billion dollars in total healthcare costs.6 1 Since 1991, the prevalence of diabetes has increased 61%.6 Regular physical activity is protective of developing non-insulin dependent diabetes through improved glucose removal and insulin sensitivity. Additionally, physical activity promotes lean muscle gain and fat loss thereby improving body composition. A dose-response relationship exists between the rate of weight loss and the frequency and duration of activity bouts, and the duration of PA programs, and the addition of physical activity to a diet only weight loss program improves long-term weight maintenance.1  The role of PA and overweight and obesity is even stronger. Overweight and obesity have become an epidemic with at least 112,000 premature deaths attributable to inactivity or diet annually.7 Overweight-related health problems account for about 5.5% to 7.0% of health expenses in the United States and $139 billion in direct and indirect healthcare costs.8, 9 National surveys, using representative samples of the U.S. population, show the prevalence of overweight (BMI = 25.0-29.9 kg/m2) and obesity (BMI > 30 kg/m2) increased dramatically among adults over the last half century, from 44.8% in 1960 to 66.3% in 2004,10, 11 with obesity rates more than doubling over the last 30 years. Sex and age-specific prevalence rates show that between 1960 and 2002 men and women from all age groups gained an average 24 pounds.12 Similar prevalence rates are found among other industrialized societies (e.g. Europe), and among urban areas in developing countries.13 These findings show that physical activity has protective effects for many diseases, even after controlling for dietary factors.  *Overweight, Energy Expenditure, and Physical Activity*  Because population-level changes in overweight and obesity resulting from environmental selection of genes would take many generations to occur, recent rapid and population specific increases in obesity are likely the result of greater energy intake and reduced physical activity. Hill et al. found that the rise in obesity rates could result from a net increase of only 100-150 calories (kcals) each day.14. While a net 150 kcal increase could be a result of increased energy consumption alone, the observed U.S. dietary trends do not support this conclusion. 15, 16 A 150 kcal daily net increase is likely to result from a combination of energy balance behaviors, including stagnant or decreasing trends of physical activity. The national recommendations of moderate activity for adults is equivalent to an expenditure of about 150 kcal/day “over and above” energy expenditure from daily activities. 17  *Physical Activity Guidelines and Definitions*  National recommendations call for adults to perform 30 minutes of moderate intensity physical activity 5 or more days per week, or 20 minutes of vigorous intensity activity 3 or more days per week, or some combination of both.18 This activity can be accumulated continuously or in short bouts of at least 10 minutes periodically throughout the day.17 Moderate intensity activity is defined as activity between 3 and 6 METs or equivalently burns 3.5 to 7 calories per minute (kcal/min). 18 Examples include brisk walking, bicycling, vacuuming, gardening, or other activities that cause small increases in breathing or heart rate. Vigorous intensity activity is defined as activity equal to or greater than 6 METs or burns more than 7 kcal/ min. 18 Examples include running, aerobics, heavy yard work, high-impact aerobic dancing, swimming continuous laps, bicycling uphill or any activities that cause large increases in breathing or heart rate where conversation is difficult or broken. Physical activity can be further distinguished by four broad categories: 1) leisure-time exercise preformed for health reasons (e.g. walking at a health club, running outdoors in evening), 2) daily living activities (e.g. cleaning the house), 3) transportation (e.g. walking to a store or bus stop), 4) occupational (e.g. lifting wood, stair use) activities.19 These four categories can include moderate and vigorous activities.  *Behavior Change Theory*  Operant, Social Learning, and Social Cognitive Theories include 3 common behavior change constructs; goal setting, reinforcement, and shaping.20-22 However, scientists using these theories vary tremendously on their operationalization of these constructs when designing interventions. For example, goals should be individualized and adaptive to participants’ current behavior repertoire.23 Most physical activity interventions adopt a target behavior that match national recommendations (e.g. 30 minutes per day) for all participants and provide reinforcement only when this goal is met. This fixed goal may lie outside of a participant’s current skills and therefore they may never attempt it or fail to reach it. Additionally, scientists may fail to program reinforcement for meeting goal or program poorly by providing incentives or rewards that are not contingent on behavior, too delayed, or infrequent relative to the behavior. Moreover, shaping behavior requires differential reinforcement, which defined as successively reinforcing greater approximations to a target behavior while systematically leaning out rewards for approximations further from the target behavior.20 Rarely is this a linear process. This requires researchers to collect repeated measures of behavior and pay attention to small improvements. Adherence to the ideals of reinforcement and shaping constructs is difficult and expensive to meet.  *Pedometer-based Interventions*  Over the last 20 years, the prevalence of people who perform no leisure time PA has remained static at about 25%, even in a context of funding and interventions to change this behavior. Of those adults who are active, the majority do not meet national guidelines.4 The most common type of leisure time exercise reported by both men and women is walking, with 44.1% of individuals walking for exercise in the past two weeks.18 Individuals report gardening as the second most common activity (29.4%). Unlike gardening, walking is a commonly accepted and highly prevalent activity that can be generalized to most subgroups (i.e. adults, seniors, overweight). Walking may be an ideal exercise behavior to target for public health interventions because it requires no additional training, equipment, or facilities, and can be accumulated through leisure-time, transportation, occupational, or daily activities. 24  *Optimal Pedometer Steps per Day.* How many pedometer steps correspond to physical activity guidelines? Hill et al. found that the rise in obesity rates could be a result of a net increase of only 100-150 calories (kcals) each day.14 The national recommendation of 30 minutes of moderate activity is equivalent to an expenditure of about 150 kcal/day, “over and above” energy expenditure from daily activities. 17 The 10,000 step criteria includes daily activities roughly equivalent to 300-400 kcal/day expenditure, varying based on body size and walking speed. 17 One study found that the 8,000 steps/day value was quantitatively linked with the 30 minute recommendation, although generalizability of this value is limited by sample characteristics and size.25 A recent review of pedometer-based studies finds that 3,000 to 4,000 steps/day “over and above” daily activities (i.e. 6,000 – 7,000 steps) should approximate the 30-minute recommendations and is in agreement with the 10,000 step/day recommendation.17  *Pedometer-based interventions*. A recent systematic review of 26 pedometer-based interventions concluded that the use of pedometers was associated with a 26.9% increase in physical activity.26 Randomized controlled trials showed stronger improvements in step counts (i.e. 2,491 steps/day over control group) after weighting by sample size. Observational studies in the review showed similar but slightly lower improvements (i.e. 2,183 steps/day). Improvements of 2,000 steps translates to about a one mile/day improvement. Pedometer interventions have also shown improvements in body mass (0.38 kg/m2 reduction compared to baseline) and systolic and diastolic blood pressure (reductions of 3.8 and 0.3 mm Hg).  Bravata et al. also examined the studies for predictors associated with improvements in physical activity. 26 Younger participants and ones with lower baseline physical activity levels showed the greatest improvements, although these characteristics were only marginally significant. *The strongest predictor of improvement was having a step/day goal.* Studies without a step goal failed to show statistically significant improvements compared to increases of over 2,000 steps/day for participants in studies with either a fixed 10,000 step/day goal or a more personalized goal. *A comparison of the number of participants who met their goals by goal type (i.e. fixed versus personalized goals) was not possible due to only two studies reporting this critical information.* However, personalized goals typically were based on incremental increases in daily steps over baseline. The authors concluded that the benefits of setting different goals remained unclear. Other predictors of physical activity improvement included participants who kept a step diary and having the intervention in a setting other than the workplace. Pedometer type was not associated with differences between studies.  *Promise of eHealth.*  Technology-based interventions promise to make individual interventions more individualized and easier to disseminate. e-Health can be defined as any interactive technology (e.g., e-mail, Internet, CD-ROM program, handheld computer, kiosk, etc.) used to change behavior.27 Interventions that incorporate technology may be able to operationalize theoretically-based behavior change components better than other types of intervention strategies. eHealth interventions may have the ability to maximize a number of theoretically important qualities common to behavior change theories. One possibility of technology is to improve goal setting by assessing smaller milestones more frequently through daily communication, and then, automatically produce new, slightly more challenging goals. For example, Croteau used technology to adjust step count goals biweekly by 5% or 10% to slowly increase daily physical activity to the desired levels, and found large and significant effects over time.28 Technology also allows delivery of specific and timely feedback.29 Two recent systematic reviews have been published on eHealth interventions related to dietary behaviors and physical activity. Kroeze et al. reviewed studies of computer-tailored materials delivered to participants without person-to-person contact (i.e., by mail, computer, or other media device).30 They found little evidence for effective computer-based PA interventions. Norman et al. identified studies for physical activity, dietary behaviors, and the combination of both behaviors.27 Norman and colleagues concluded that results were mixed for activity and better research was needed to determine how technology could enhance behavioral outcomes. In particular, the lack of consistency in eHealth intervention outcomes could be explained by a lack of theoretical fidelity or poor study designs.27  *Summary*  Regular physical activity is associated with prevention of morbidity and mortality. Yet, a large proportion of the population does not meet the recommended PA guidelines. This may be a result of an imbalance between behavioral consequences for sedentary behavior compared to PA behaviors. Walking is a highly accepted physical activity behavior that all age groups can adopt. Individual-level behavioral interventions have had limited success explaining PA variance and changing PA behaviors. This limited effect may be partially due to a lack of theoretical guidance and intervention theoretical fidelity. eHealth interventions may allow behavioral scientists to improve intervention theoretical fidelity resulting in increased PA among inactive individuals. |

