| 1. List the criteria for inclusion and exclusion of subjects in this study. Provide a rationale to support the selection criteria.  b. Describe the screening procedures used to determine subject eligibility. Identify how the inclusion and exclusion criteria will be assessed and by whom. For studies that identify specific inclusion and exclusion requirements to determine subject eligibility (e.g., age, physical or psychological condition), append a screening checklist in which specific inclusion and exclusion criteria are listed and defined.  c. Describe how data collected during screening will be handled if the person is found to be ineligible.  d. Describe procedures used to obtain consent from the person in advance of implementing the screening procedures. Please refer to sections 4.8 and 4.9 of the IRB Guidebook for guidance on subject selection and screening procedures.   To qualify as a research study participant, individuals must: 1) live in San Diego County, 2) be between 18 and 55 years old, 3) currently not exceeding 1,000 MET-minutes per week of physical activity determined by the International Physical Activity Questionnaire (IPAQ short form), 4) not suffering from a medical condition or taking medication(s) that would prohibit one from adopting a moderate intensity physical activity program, 5) have a body mass index between 25 and 35 kg/m2, 6) not currently pregnant, 7) familiar with email and access to email and the internet daily, 8) not planning to leave San Diego County for more than 10 days over the next 6 months, and 9) not planning to move away from San Diego County in the next 6 months. The telephone screening form will be used to assess whether individuals meet the inclusion criteria. A copy of the screening form has been included with this application  These inclusion and exclusion criteria aim to balance the ideals of recruiting a representative sample and identifying individuals with a high probability of being able to participate and complete the 6 month study. The Physical Activity Readiness Questionnaire (PAR-Q), a physical activity health screener, will assess candidates’ health status for the adoption of an exercise intervention (Thomas, Reading, & Shephard, 1992), and the International Physical Activity Questionnaire (short form) will determine physical inactivity status (Craig et al., 2003). Adults classified as class 2 obese (BMI≥35), older than 55 years of age or using medications that prohibit physical activity will be excluded because of the increased probability that other known and unknown variables could affect the efficacy of the intervention. Such variables can include a higher incidence of cardiovascular diseases, cancers, bone fractures, medication use, death, or other life events.  If a participant is found to be ineligible for the study, their screening information will be kept for up to 1 year. Data from ineligible subjects will be aggregated and used to summarize and compare characteristics to that group who qualified.  We are requesting approval to use verbal consent instead of written consent for the telephone screening of potential subjects. The telephone screening will be used to determine if individuals quality for inclusion into the study. During the telephone screening phone call, participants will be provided a brief overview of the study, informed of the risks involved in answering the screening questions for eligibility, provided telephone number of the PI and SDSU Human Research Protections Program Office, and asked if they would be willing to complete the eligibility screening call. This information is provided on the first page of the telephone script. If an individual qualifies for the study, he or she will be invited to the research office, and, at that time, the study and risks and benefits will be reviewed once again. Written informed consent will be obtained before participation in the 6-month study begins. |

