# Research Design and Methods

Description of Research Design

| Describe the research design, the scientific rationale underlying the proposed research and the statistical basis for the structure of the investigation. Specify aims of the research that include the hypotheses to be tested, questions to answer, data to be gathered and tested. Describe procedures used to test the hypotheses. Provide enough information about the research design to allow the IRB to make an informed judgment that the design will allow you to answer your questions and produce valid results. This information is critical to the IRB in weighing the potential benefits of the study as compared to the potential risks. Please refer to section 4.13 in the IRB Guidebook for information on IRB review of research design.  *Research Design.*  This study aims to test an adaptive goal setting intervention with frequent reinforcement (ActiveRewards intervention) to increase the number of steps/day to recommended guidelines for inactive adults by comparing to a fixed goal setting physical activity intervention. The study will be conducted with 30 participants using a two-group randomized controlled trial design with repeated pedometer measures over 6 months. The each group will experience two phases during the study consisting of a no-intervention baseline phase and one of two intervention phases. 31  *Baseline Phase.* Participants in both groups will be asked to wear a sealed Omron HJ-720ITC pedometer for the first 10 days of the study to collect baseline measures of physical activity. The pedometer will be masked with tape to obscure the number of steps taken. This will be done to reduce participant reactions to the pedometer, which will allow for a shorter baseline phase. Participants will remove the tape seal and report their steps via email after 10 days. After completing the baseline phase, participants will be randomized into either the ActiveReward or Comparison intervention groups.  The intervention components for both groups are shown in the table below. Both groups will receive similar components: 1) a pedometer, 2) self-monitoring of physical activity, 3) brief educational materials, 4) motivational prompts, 5) physical activity goals, and 6) voucher incentives.    *•• Pedometer Assessment.* Participants in both groups will be provided an Omron (HJ-720ITC) pedometer on the first day of the baseline phase, and will continue to use the pedometer throughout the entire study. The HJ-720ITC is small 1 7/8''(w) × 2 7/8''(h) × 5/8''(d) lightweight (less than 1.5 ounces) device and can be worn on a participants’ waistband or belt or kept in their pocket. The device is accurate within 3% of actual steps taken.32  *•• Self Monitoring.* Participants will use the pedometer to record the number of steps they accumulate each day. ActiveReward participants will self-report their accumulated steps to the intervention staff each day via email. It is expected to take less than 5 minutes to write an email to report each day. Comparison Group participants will report their steps weekly via email; this should take less than 20 minutes each week. We plan to make reporting easier by requiring participants to report only their ID number, the date, and steps taken. This should limit response burden.  *•• Physical Activity Education Component.* On the first intervention day, participants in both groups will be sent via email two brochures on physical activity. One was entitled, “Be Active Your Way: A Guide for Adults” published by the U.S. Health and Human Services and available at the Centers for Disease Control and Prevention website (www.cdc.gov) (Department of Health and Human Services, 2008). The publication defines physical activity and covers the national recommendations for adults. It also included a number of sections tailored to individuals’ current activity status. These sections included, “Getting Started with Physical Activity”, “Making Physical Activity Part of Your Life”, “Keeping It Up, Stepping It Up” and “Being Active for Life”. The second brochure was entitled, “100 Ways to Add 2000 Steps” by the America on the Move Foundation (www.americaonthemove.org) (America On the Move, 2008). This brochure suggests 100 ways to increase steps throughout the day with the caveat that following only one tip would not provide 2000 additional steps. Tips included “Take your dog for a walk”, “Take an aerobics step class”, “Walk around the outside aisle of the grocery store before shopping”, etc. America on the Move provides these materials free of charge to health professionals and researchers. No further educational materials will be provided to participants. Reviewing these materials is expected to take about 1 hour. The brochures are included with this IRB application.  *•• Motivational prompts.* Participants will receive motivational prompts about their physical activity to help encourage change. It is estimated that one message will be delivered every 2 weeks and participants can chose to receive these via email or text message. The prompts will include motivational messages, reminders about the health risks and benefits of physical activity, and encouraging advice developed by the PIs or research assistants. These prompts may overlap with the messages communicated in the educational component or prompt individuals to re-review the educational brochures. Both groups will receive the same prompts. Reviewing prompt messages is expected to take less than 1 minute each occurrence.  *•• Physical Activity Goals.* Both groups will receive physical activity goals, but groups will differ on the types of goal. The Comparison group will be instructed to try to meet the standard ‘usual care’ goal of at least 10,000 steps each day on at least 5 days per week. This represents a constant and fixed goal to attempt to achieve. As noted in the background selection, this goal approximates the national physical activity recommendation when activities from daily living are included in the count. This goal is commonly heard in the media and has been adopted by physical activity advocacy groups (e.g. America on the Move Foundation). Participants will receive this goal on the first intervention day and will be reminded of it periodically.  ActiveRewards group participants will be prescribed personalized, adaptive goals based on a 10-day moving sample window of their past physical activity measured by the pedometer. Participants will be informed that the goals adapt to their performance. Once a participant emails their pedometer steps, the research staff will send the next day’s step goal via email. Since the goals will adjust daily, each step goal will only good for that day. The percentile algorithm will determine new steps goals.  *•• ActiveRewards Goal Setting Algorithm.* Prior studies using pedometers and goal setting have prescribed goals for participants to meet by adding some progressive amount to participants’ baseline level or have provided a fixed goal, such as 10,000 steps per day, based on guidelines associated with national physical activity recommendations. To our knowledge, no studies to date have applied a continuously adaptive goal-setting algorithm based on participant’s own behavior.  The concept we plan to test is based on percentiles. The Percentiles algorithm requires: 1) continuous and repeated assessments of behavior, 2) rank that sample of behavior from lowest to highest, and 3) apply percentile to that distribution to determine the goal. For example, for one participant, the step count each day for the last 10 days (ranked from lowest to highest) was 1000, 1500, 2600, 4500, 5000, 5700, 6300, 6500, 8000, 11,000. This identifies the distribution of step counts. We plan to use a 70th percentile criterion with a moving 10-day window. Based on this distribution, a goal of 6,300 steps (70th percentile of the distribution) would be provided for the 11th day. Meeting or exceeding this goal would earn a reward voucher for that day. Each new day’s step count will be used to replace the oldest observation of the 10 days, re-rank the distribution, provide a new goal, and slowly but progressively increase participant’s activity behavior over time by always rewarding the top 30% of the distribution of behavior. The algorithm is adaptive, meaning that as physical activity behavior vacillates uniquely for each individual, the algorithm increases or decreases the absolute number of steps so that the goal always represents the best 30% of the last 10 days. Participants will be provided a new goal each day during the intervention phase of the study. **It is important to highlight that prescribed goals will always fall within each participant’s abilities based on a known sample of their behavior from the last 10 days. This is unlike the usual care goal of at least 10,000 steps 5 days per week, which is likely beyond their current abilities.**  One feasibility study to date tested a percentile algorithm for physical activity.33 [name] used a 40th percentile and found a 17% increase in steps/day and 32% increase in their moderate-to-vigorous physical activity minutes/day over baseline. At present, we do not know the specific percentile that will produce optimal change for physical activity behavior. Higher percentiles (e.g. 90th percentile) risk the possibility that a participant may never meet the goal since only best 10% of a participant’s behavior would meet it. As found by contingency management studies aimed at decreasing substance use, this could lead to participants experiencing frustration at the difficulty of the behavior change goals, and lead participants to drop out of the study early.34 A 5th percentile would be too easy and while this would produce consistent physical activity at some level, it would not result in longer bouts of physical activity.  *** Reward Vouchers.* ActiveReward Group participants will earn one reward point each day they reach their step goal over the 6 months. This incentive system is similar to “credit card membership reward points” that can be exchanged for various items and services. Each point will be worth $1.00. It is expected that participants will meet the programmed average of 30% of goals over the course of the intervention. This equals between $52 and $69 (+10% to be conservative) in incentives over the course of the intervention phase. Participants can bank their vouchers to save for larger payouts (e.g., $10 voucher). Participants will not earn or lose vouchers for missing a daily goal or failing to report step counts. Banked vouchers will never be subtracted. Vouchers will be sent electronically in the form of gift cards that can be exchanged after accumulating a minimum of $5 ($5 is the minimum size gift card at many companies). Electronic vouchers will be sent immediately and will be available for a select number of retailers (e.g. Apple iTunes, Amazon.com) or donation websites (e.g American Red Cross, Kiva.org). Participants in prior studies have requested an option for donation websites.  The Comparison Group will receive $70 in incentives during the intervention phase, but instead of earning for accomplishing physical activity goals, they will receive a progressively increasing amount for exchanging their pedometer each month (pedometers need to be exchanged because they only have 40 days of internal memory). Comparison group participants will a total of $70 on the following schedule: $5 for month 1, $10 for month 2, $10 for month 3, $20 for month 4, $25 for month 5. Both Groups will receive $20 for completing the 6-month questionnaire and returning the pedometer.  Finkelstein et al. found that participants who earned $7.00 for every 1% decrease in body fat lost an average 1.5% of their body weight (or 3 pounds for their 200 pound average participant) by the first opportunity earn the reward at 3 months (Finkelstein et al., 2007). In comparison, the current study offers $1.00 for each instance that participants meet their daily personalized goal which was usually less than 10,000 steps. As noted earlier, 10,000 steps/day is equivalent to 5 miles of walking. A 200 pound individual walking five miles at a moderate intensity (i.e. MET = 3.0) would take about 100 minutes and expend about 455 calories, and would earn $1.00. After matching on calorie expenditure, the current study offers an incentive about 119% more (Finkelstein et al.: 10,500 kcal = $10.50; current study: 10,500 kcal =$23.00) for the same calories expended (assuming a fixed caloric intake). However, the current study will not usually prescribe goals this difficult, so this difference could be greater. Nevertheless, compared to Finkelstein et al., the current study maximizes the fidelity of incentives by: 1) providing opportunities to earn smaller rewards more frequently (i.e. a $1 reward each day versus $7 every 3 months), 2) using a direct contingency of reinforcement for physical activity - instead of weight loss, which can include a number of desired and undesired behaviors, and 3) has a shorter latency between the occurrence of physical activity bouts and the presentation of the reward (i.e. the same day versus 3 months later for the Finkelstein et al. study).  **Statistical Considerations**  Our null hypothesis is that the ActiveRewards Intervention group will not differ in their average steps/day change compared to the Comparison intervention over the course of 6 months. The alternative hypothesis is that ActiveReward participants will show greater improvements in their physical activity change compared to the Comparison Group. Specifically, a mean difference of 1,000 steps/day between groups will be considered practically important. This effect is lower than the mean change observed by a recent systematic review of pedometer interventions but realistic given the pilot nature of the current study .26 Because this is a pilot test designed to test the feasibility of using percentiles for promoting exercise, we plan to recruit 30 participants into the study. Thirty individuals is estimated to be sufficient sample to test the concepts and determined to be financial feasible. The pilot study will test the intervention efficacy (i.e., ‘proof of concept’) and will be a preliminary study for future grants to explore this line of research.  **Data Analysis**  **Aim #1.** **To determine whether physical activity (pedometer-measured steps/day) in both the ActiveRewards and Comparison groups increased compared to their respective baseline levels.** We plan to analyze this aim using descriptive and visual methods. Means, standard deviations, and other descriptive data will be summarized by group and intervention phase. Pedometer data will be plotted on a time-series graph and phases delineated to evaluate the change in level, slope, and variability between the baseline and intervention phases of the study for all 30 participants independently and their group means. Regression models may be used to explore change by phase for each group. It is expected that each intervention phase will produce changes in the average number of steps taken per day.    **Aim #2. To evaluate whether the ActiveRewards intervention results in greater change in physical activity (steps/day) relative to the Comparison group.** Since there will be 6 months of daily pedometer data, a multi-level random-effects regression analysis will allow us to detect differences between intervention groups. The independence of observations assumption of many statistical tests are violated with time series data because repeated measures of behavior tend show serial dependence.35The multi-level random-effects analysis will allow us to use all of the available time-unstructured data from the sample of participants without imputing missing values, thus allowing for a smaller sample size. This modeling approach will also allow us to explore the autocorrelation that exists with repeated measures data.36 As noted earlier, a difference of 1000 steps/day between groups would be considered a practically important outcome. |

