• Satisfaction with Intervention Modality. At the 6 month intervention, participants will be asked to rate how motivating or burdensome specific study components were to them, and their overall satisfaction with the study. Participants will also asked about their personal experience with the intervention, any side effects or injuries, and their recommendations for improvement. This consumer satisfaction may be helpful for understanding how participants experienced the study, and for improving the intervention (Winett, Moore, & Anderson, 1991).

• Demographic and Socioeconomic (SES) Variables. Demographic variables including sex, ethnicity/race, age, highest educational achievement and household income, will be collected from participants during the phone screening.

• Neighborhood type.Urban form and neighborhood characteristics will be measured using the Neighborhood Environment Walkability Scale (NEWS). The survey includes eight sections measuring self-reported neighborhood residential density, proximity to nonresidential land uses, access to services, street connectivity, walking and cycling facilities, aesthetics, traffic safety, and crime safety. The NEWS has shown good to excellent test-retest reliability and is able to accurately discriminate high and low walkable communities.38-40

• Self-reported physical activity. The International Physical Activity Questionnaire (IPAQ) short form will be used to measure physical activity at baseline to determine whether participants perform less than national MVPA recommendations. The IPAQ asks participants to report their frequency and duration of light, moderate, vigorous, walking, and sitting activities over the last 7 days. The IPAQ has shown to be a reliable and valid measure of physical activity with adult populations.19

Study Location

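### The IPAQ eligibility cut of 1,000 MET-min/week lies above the protocol's own national recommendation, so it does not exclude adults who already meet that recommendation

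*Protocol*

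**What the plan says.** The Subjects section (Selection Criteria and Participant Screening) sets the upper limit of activity: candidates must be "currently not exceeding 1,000 MET-minutes per week of physical activity determined by the International Physical Activity Questionnaire (IPAQ short form"). The same section says the IPAQ "will determine physical inactivity status".

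Research Instruments, under self-reported physical activity, says the IPAQ is used at baseline "to determine whether participants perform less than national MVPA recommendations". It describes the instrument as collecting frequency and duration of light, moderate, vigorous, walking and sitting activity over seven days.

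The Statement of Purpose and Background defines the benchmark: "National recommendations call for adults to perform 30 minutes of moderate intensity physical activity 5 or more days per week", or 20 minutes of vigorous activity on at least 3 days, or a mixture. It adds: "Moderate intensity activity is defined as activity between 3 and 6 METs". Vigorous activity starts at 6 METs.

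Research Design and Methods states the aim as "to increase the number of steps/day to recommended guidelines for inactive adults" and says of the Comparison arm's goal of 10,000 steps on 5 days a week that it is one "which is likely beyond their current abilities".

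**The concern.** The screen has a stated job: to find inactive adults who fall short of the national recommendation. If its threshold is higher than the recommendation, it cannot do that job.

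Two things are then at stake. Conclusions would be worded for inactive adults below guidelines when the sample may include people who already meet them. And the design rationale, that a fixed 10,000-step goal is probably too hard for these participants while an adaptive goal is not, would not be secured by the entry criteria. With 30 participants, a few people already near the fixed goal would be a visible share of the sample.

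**Working it through.** The protocol gives no derivation of 1,000, so there is no calculation of its own to reproduce. The check converts the recommendation to the unit of the cut: MET-min/week = METs × minutes per day × days per week.

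**Inputs, all from the protocol:** 30 min on 5 days at 3 to 6 METs; 20 min on 3 days at 6 METs or more (both Background); cut 1,000 (Subjects).

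**Recommendation against the cut**

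| Route, at its minimum | Calculation | MET-min/week | 1,000 divided by this |
|---|---|---|---|
| Moderate, 3 METs | 30 × 5 × 3 | 450 | 2.2 |
| Moderate, 4 METs | 30 × 5 × 4 | 600 | 1.7 |
| Moderate, 5 METs | 30 × 5 × 5 | 750 | 1.3 |
| Moderate, 6 METs | 30 × 5 × 6 | 900 | 1.1 |
| Vigorous, 6 METs | 20 × 3 × 6 | 360 | 2.8 |

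No row reaches 1,000. For 150 min/week to exceed the cut, the average would have to be above 1,000 / 150 = 6.7 METs, outside the protocol's moderate range. For 60 min/week it would have to be above 1,000 / 60 = 16.7 METs. Read the other way, the cut allows 1,000 / 3 = 333 min/week at 3 METs, or 1,000 / 6 = 167 min/week at 6 METs, against a recommended 150.

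**What the cut means in steps.** Research Design and Methods equates 10,000 steps with 5 miles, taking about 100 minutes at 3.0 METs for a 200-pound person, so about 100 steps/min. Its energy figure for that walk is consistent: 90.7 kg × 3.0 × 100/60 h = 454 kcal, against 455 stated. Then 1,000 / 3 / 7 = 47.6 min/day, and 47.6 × 100 = about 4,760 steps/day.

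- If every step is reported on the IPAQ, the limit is about 4,760 steps/day. Someone walking 10,000 steps on 5 days would score 100 × 3 × 5 = 1,500 and be excluded.
- If none of the 6,000 to 7,000 daily-activity steps given in the Background is reported, the limit is 4,760 + 6,000 to 7,000 = about 10,760 to 11,760 steps/day. Someone reaching 10,000 through 3,000 to 4,000 extra steps on 5 days would score 30 to 40 min × 3 × 5 = 450 to 600 and be eligible.

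The protocol does not say which counting applies.

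**Other safeguards.** The selection criteria contain no second inactivity test. The sealed 10-day baseline comes before randomisation, but no step ceiling is attached to it.

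**The case against.** The strongest reply is that unlike quantities are being compared. The Background treats the recommended dose as additional to daily living, while the IPAQ covers light activity and walking as well. A ceiling on total activity may reasonably sit above the guideline dose, and someone scoring close to 1,000 need not meet the guideline. This stands, and it limits the point: not everyone under the cut is active. It does not rescue the cut, because a person who does the recommended minimum and reports little else still passes.

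The protocol also states its criterion openly, hedges the remark about participants' abilities, and describes its criteria as broad, in a small pilot. That is fair, but the stated purpose in Research Instruments remains unmet.

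A reader might go further and infer that the loose cut tilts the comparison toward ActiveRewards. The documents do not support this. Randomisation follows the baseline phase, so active participants are equally likely in either arm; the adaptive goal can fall as well as rise; and the fixed goal is a minimum, not a ceiling. Poor fit of a fixed goal to the individual is part of what the trial compares.

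A reader might also infer that participants at the limit are already above 10,000 steps. That is only the upper end of the range.

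**Conclusion.** The cut does not deliver the selection the protocol assigns to it. This holds at every MET value in the protocol's moderate range and at the vigorous floor, and it needs no scoring weights from outside the document. The gap is 100 to 550 MET-min/week on the moderate route (1,000 − 900 to 1,000 − 450) and 640 at the vigorous floor (1,000 − 360).

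The consequence is one of interpretation: which population the result applies to, and whether the fixed goal was in fact out of reach for those enrolled. The validity of the randomised contrast is not in question. How many already-active adults would enrol cannot be derived from the protocol. The step range of about 4,760 to 11,760 per day rests on 3 METs, 100 steps/min, all reported activity being walking, and an unstated rule on routine walking.

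**What to change.** Reconcile the selection criterion, the statement of target population in Research Design and Methods, and the stated purpose of the IPAQ in Research Instruments. Either of two routes would do.

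1. Apply the recommendation directly at screening, using the days and minutes that the IPAQ already collects, and state how walking and mixtures of moderate and vigorous activity count. Cost: some more volunteers are screened out. The protocol expects no major recruitment problem, since most adults fall below the recommendation.
2. Keep 1,000, word the population and conclusions as adults reporting at or below 1,000 MET-min/week, and drop the claim that the screen selects people below the national recommendation. Report sealed-baseline steps/day by arm, including how many participants were already at 10,000. Cost: wording and one descriptive table from data already being collected.

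Moving the cut to somewhere between 450 and 900 would not be enough. It would still admit people who meet the recommendation by the vigorous route at 360, or by moderate activity at 3 METs, and on an all-activity total it could exclude inactive adults who report routine walking: 450 / 3 / 7 is only about 21 min/day.
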